#### Exclusion criteria

Heart failure due to left ventricular systolic dysfunction (LVSD) prescribed only ACE inhibitors/angiotensin II receptor blockers and/or beta-blockers and/or spironolactone (removing any of which would be contraindicated).Heart failure diagnosis without a coded echocardiogram (might have undiagnosed LVSD and a compelling need for ACEI/angiotensin II receptor blocker and beta-blockers).Suffered a myocardial infarction or stroke within the past 6 months.Secondary hypertension or previous accelerated or malignant hypertension.Lacking capacity to give consent and without a Personal Legal Representative present at the point of screening.Investigator deems that there is a compelling indication for medication continuation.Participating in any other randomised controlled trial of drug treatment or interventional medical devices in the past 4 weeks (can be re-invited subsequently).

The participant journey through the trial is described in Fig. 1. Those potential participants who respond to an invitation attend a baseline visit at their general practice. At this visit, the general practitioner (GP) (or qualified and appropriately trained health professional responsible for hypertension care or medicines management) explains the trial and gives time to answer any questions. Following this, if they are happy to proceed, they will be asked to give informed consent. The trial aims to include vulnerable individuals, including those with dementia and those lacking capacity to consent for themselves. In these instances, consent from an appropriate Personal Legal Representative is requested.

**Fig. 1 Fig1:**
[figure not shown]
Trial flow diagram. GP, general practitioner; the 4-week safety visit is repeated each time a medication is withdrawn

### Baseline assessments

After consent, participants undergo baseline procedures with a research nurse, or other appropriately trained and delegated member of the team, including measurement of clinic blood pressure readings. Blood pressure is taken after participants have been seated for 5 min of rest using a clinically validated blood pressure monitor, and the mean of the 2nd and 3rd readings is used the define trial eligibility. To test for orthostatic hypotension, two further readings are taken in the standing position, immediately, and after 3 min [23]. Once eligibility is confirmed, the participant then completes the trial questionnaires including the Illness Perception Questionnaire (symptom list) [24], Multimorbidity Treatment Burden Questionnaire [25], Katz Activities of Daily Living (ADL) - Life Ability Questionnaire [17], and Beliefs about Medicines Questionnaire (BMQ) General [15] and the EQ-5D-5L [16] which will give an interpretation of quality of life. Also included is an adapted variant of the Client Service Receipt Inventory [26] to measure health economic burden, the Free-Cog [27] to assess cognition, and the Attitudes Towards Deprescribing Questionnaire [28] to determine patient perception of medication reduction. Once these questionnaires have been completed to the best of their ability, they are then randomised into the trial by the person performing the baseline procedures. Stratified randomisation is used to individually allocate participants (1:1) to one of the two trial groups using a fully validated web-based randomisation system (Sortition) with stratification factors age (i.e. 75–79 and ≥ 80 years) and region of England. Randomly permuted block sizes is used within strata.

### Intervention and comparator groups

The intervention is step-down antihypertensive medication reduction in comparison with usual care. Those in the intervention arm have antihypertensive medications removed one at a time under the supervision of the GP/prescriber, maintaining a systolic blood pressure of less than 140 mm Hg (in those aged 75–79 years) or 150 mm Hg (in those aged 80 + years). GPs/prescribers are given guidance on how to choose medications for deprescribing, outlined in Fig. 2, in line with approaches taken in previous studies [29, 30], but the final decisions on which drug to withdraw are left to them. This decision about which medications to remove is detailed in a medication reduction plan (prepared ahead of the baseline visit). Participants randomised to medication reduction will be informed which medication the GP has recommended for deprescribing and be asked to return it to their local pharmacy. There are no validated instruments for measuring compliance with medication reduction. GP prescribing data will be collected from electronic health records as a measure of compliance with the trial protocol. Those allocated to the control group receive usual clinical care, with no medication changes mandated. The trial uses an open-label design, so patients and practitioners are not blinded to the intervention or endpoints. Analysis of outcomes is blinded to the intervention allocation.

**Fig. 2 Fig2:**
[figure not shown]
Antihypertensive deprescribing algorithm. ACE, angiotensin-converting enzyme; COPD, chronic obstructive pulmonary disease; LVSD, left ventricular systolic dysfunction; BP, blood pressure

To maintain fidelity of the intervention, each medication is completely stopped, regardless of type or dose. Gradual dose reduction is not warranted, since any effects of withdrawing medication will be captured at the 4-week safety visit. The only exception to this is when withdrawing beta-blockers or clonidine, where the dose can be reduced first to avoid rebound adrenergic hypersensitivity.

### Follow-up

All participants (regardless of randomised group) are asked to return to their GP practice approximately 4 weeks following the baseline visit to have their blood pressure checked, and to report any adverse events that may have occurred. To ensure the safety of participants, blood pressure readings are taken in person. For those in the intervention arm whose blood pressure remains well controlled up to a target blood pressure of < 150 mmHg (or < 140 mmHg for those 75–79), the person performing the visit refers to the medication reduction plan and deprescribes a further antihypertensive if indicated. If another medication is deprescribed, participants are asked to attend a further safety visit 4 weeks later. This is repeated until there are no further antihypertensives to deprescribe, or until the GP/prescriber or participant feel it is inappropriate to deprescribe further. If participants’ blood pressure has risen above target at the safety visit, site staff are advised to invite them for another visit 1 week later to recheck their blood pressure. If the readings are still above threshold, further monitoring or re-prescribing of withdrawn medication is at the clinician’s discretion.

All follow-up after the safety visits are conducted remotely. Patient-reported outcomes are collected via questionnaires completed 1 year after participant’s baseline visit, which are either sent via email or post depending on individual participant preference. Clinical outcome data is extracted from electronic health records using three approaches. Firstly, primary care data is collected directly from participant’s records via a purpose-built database search run in each participating practice at the end of follow-up. Secondly, all participants are linked using unique trial identifiers, NHS number, and one other identifier (date of birth) to data held by NHS England. This includes Hospital Episode Statistics (the commissioning dataset that captures hospital activity such as diagnoses, procedures and therapies nationally) and Civil Registrations of Death, as provided by the Office of National Statistics. Thirdly, where possible and appropriate, primary care data is extracted remotely from the electronic health records of participants registered at primary care sites contributing to the Oxford Clinical Informatics Digital Hub (ORCHID).

### Safety reporting

Given the vulnerable nature of the population, adverse events are expected to be very common and usually unrelated to the intervention of interest. As a result, formal safety reporting is limited to those adverse events deemed related to antihypertensive medication reduction (adverse drug withdrawal events or ADWEs) or considered serious, as determined by the GP (or qualified and appropriately trained health professional responsible for hypertension care or medicines management). Adverse events of interest for this trial are those relating to fractures or falls, the circulatory system, kidney problems, electrolyte abnormalities, or hypotension/syncope. Adverse events occurring during the active follow-up period of the trial (1 year from randomisation for each participant) that are observed by the Investigator or reported by the participant or their carer are reported on the trial CRF, whether or not attributed to trial medication.

The following events are exempt from serious adverse event reporting procedures:Admission to hospital for routine, planned medical procedures or health assessment (e.g. hip replacement, routine transfusions).Admission to hospital or prolongation of hospitalisation for any reason other than for health purposes (e.g. prolongation of hospitalisation while appropriate social care is set up).Hospital visits for < 24 h that do not result in in-patient admission, unless considered an important medical event.

### Trial committees

The OPTIMISE2 Trial Management Group (TMG) is responsible for the monitoring of all aspects of the trial’s conduct and progress, and will ensure that the protocol is adhered to and that appropriate action is taken to safeguard participants and the quality of the trial itself. The TMG comprises individuals responsible for the trial’s day-to-day management (e.g. the Chief Investigator/Trial Lead, Trial Manager, Statistician, Data Manager) and will meet at least monthly throughout the course of the trial.

A Trial Steering Committee (TSC) provides overall supervision of the trial and ensures the trial is conducted in accordance with the principles of GCP. The TSC includes at least 75% of members who are independent of the investigators, including an independent chairperson. An independent Data Monitoring & Ethics Committee (DMEC) reports to and advises the TSC and includes two independent physicians and a statistician. The DMEC and TSC convene at 6-monthly intervals with sufficient time between each committee for the DMEC’s findings to be sent to the TSC ahead of their meeting. They will review the accruing trial and safety data to ensure trial site staff and participants are aware of any relevant safety information and to determine whether any reasons exist for the trial to be discontinued.

### Data management

The data management aspects of the trial are fully described in the Data Management Plan. This trial uses the RedCap eCRF system, where data are stored on secure servers with user access and logins controlled by our data manager. Access to the database is granted only after receipt of the database training log. Within the database, participants are identified only by a unique Trial ID, which is generated for every participant enrolled in the trial. The trial databases include secure login for staff at participating sites and facilities for manual entry of data and upload of files where appropriate. Single data entry is used in this trial, with automated checks built into the database that fire upon entry of data.

All data is stored within the database until all analyses have been completed, in compliance with the University of Oxford standard operating procedures for data retention. On completion of the trial and data cleaning, the trial documentation will be transferred to a secure, GCP compliant archiving facility, where it will be held for at least 5 years.

### Participant confidentiality

The trial complies with the UK General Data Protection Regulation (GDPR) and Data Protection Act 2018, which require data to be de-identified as soon as it is practical to do so. The processing of the personal data of participants is minimised by making use of a unique participant trial number only on all trial documents and any electronic database(s) (excluding consent forms). All documents are stored securely and only accessible by trial staff and authorised personnel. The trial staff safeguard the privacy of participants’ personal data.

### Sample size

The trial aims to randomise 3,014 participants and actively follow them up for 1 year to determine whether there is a non-inferior difference in death or first emergency hospital admission between treatment groups. This sample size gives 90% power to demonstrate a non-inferiority margin of 5%, at a 2.5% 1-sided level of significance, allowing for a 5% loss to follow-up.

This is based on a rate of emergency hospital admissions in the usual care group of 20.7% at 12 months, based on previously reported rates from HES data [31] inflated by 1% to take into account those people that die without a preceding emergency admission [32]. Due to the efficient trial design being employed, where most outcomes are measured using linked electronic health records, minimal loss to follow-up is expected. However, the sample size does include adjustment for up to 5% loss to follow-up, in the event that patients withdraw completely or records cannot be linked, based on the previous trial (where 1.4% of participants were lost to follow-up) [12].

### Statistical methods for primary and secondary outcomes

The primary analysis will be according to randomised treatment assignment and will include all randomised participants for whom data are available, as defined by protocol eligibility criteria. Deprescribing antihypertensive medication will be deemed non-inferior to usual care in terms of death or emergency hospital admission if the lower limit of a 95% confidence interval for the absolute risk difference between usual care and medication reduction groups is above − 5%, i.e. if the percentage of emergency hospitalisations/deaths in the deprescribing group is less than 5 percentage units higher than in the usual care group. This primary outcome will be analysed using a generalised linear mixed effects model. The response will be a binary indicator of whether the participant experienced death or emergency hospitalisation at 1 year. The model will include age and NHS England region as fixed effects and site as a random effect. Any covariates found to be predictive of missingness in the outcome, through fitting univariate logistic regression models, will be included in the model.

Generalised linear models adjusting for age as a fixed effect and site as a random effect will be used for secondary outcomes e.g. differences in the proportions of patients with serious falls, serious hypotension, syncope, fracture, hospitalisation/death, any non-serious adverse event, ADWE, all-cause death, major cardiovascular events, stroke, MI and perceived side effects to antihypertensive at 12 months, differences in mean change in treatment burden score, number of prescribed medications, number of prescribed antihypertensives, blood pressure, quality of life at 12 months.

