#### Inclusion criteria

Willing and able to give informed consent for participation in the trial (or with personal legal representative consent)Willing and able to report any safety concerns or with a suitable carer able to report these if unableRegistered at either a practice using electronic health record systems (e.g. EMIS or SystmOne) or contributing to or willing to contribute to The Oxford Clinical Informatics Digital Hub ORCHID [18].Aged 75 years or above at recruitment.Controlled systolic blood pressure, defined (in accordance with NICE 2019 guidelines) [9] as less than 140 mmHg (if aged 75–79 years) or less than 150 mmHg (if aged 80 years or above). Systolic blood pressure level will be based on screening measurements taken at baseline (mean of the 2nd and 3rd readings taken in a standardised manner) [19] or from patient records if a face-to-face baseline visit is not possible.Prescribed two or more antihypertensive medications for at least 12 months prior to trial entry. Antihypertensive medications defined as any ACE inhibitor, angiotensin II receptor blocker, calcium channel blocker, thiazide and thiazide-like diuretic (including loop diuretics), potassium-sparing diuretic, alpha-blocker, beta-blocker, vasodilator antihypertensives, centrally acting antihypertensives, direct renin inhibitors, adrenergic neurone blocking drugs.Stable dose of antihypertensive medications for at least 4 weeks prior to trial entry.Moderate or severe frailty (defined by an eFI score ≥ 0.20) [20] and/or high risk (> 5%) of hypotension, syncope or falls in the next 5 years, based on STRATIFY risk prediction algorithms [21, 22] applied to an individual’s electronic health record.

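### Extra covariates enter the primary model only because they predict missing outcomes; a fixed set including the eligibility risk scores would be sounder and slightly more precise

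*Protocol article*

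**What the plan says.** Under Statistical methods for primary and secondary outcomes, the protocol article specifies a generalised linear mixed model for the binary 1-year outcome, with age and NHS England region as fixed effects and site as a random effect. It continues: "Any covariates found to be predictive of missingness in the outcome, through fitting univariate logistic regression models, will be included in the model". Non-inferiority is judged on the absolute risk difference, using a 95% confidence interval against a 5-point margin. The analysis is to include every randomised participant with data.

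Three other sections bear on this rule:
- **Sample size.** Because outcomes come mainly from linked records, "minimal loss to follow-up is expected". Loss was 1.4% in the previous trial, and 5% is allowed for here. No covariate adjustment is mentioned.
- **Baseline assessments.** Randomisation follows the questionnaires and the cognitive test: "Once these questionnaires have been completed to the best of their ability".
- **Inclusion criteria.** Entry requires an eFI of at least 0.20 and/or a 5-year risk above 5% of hypotension, syncope or falls, "based on STRATIFY risk prediction algorithms" applied to the health record. Neither score is named in the primary model.

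**The concern.** The covariate set of the confirmatory model is not settled until the pattern of missing outcomes has been seen, and the criterion for entry is the wrong one. In an available-case analysis, adjusting for a predictor of missingness reduces bias only if that variable also predicts the outcome, and precision improves only if it is prognostic. The rule tests neither. A candidate list and a threshold in the statistical analysis plan would not change this, because the article itself fixes the criterion.

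The rule could also work against its purpose. The outcome is expected to be nearly complete, while some baseline measures may not be: the trial admits people with dementia or without capacity, and questionnaires are filled in as far as each person can manage. A regression on an incomplete covariate drops those rows unless their missing values are handled.

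Meanwhile, two record-based scores that plausibly predict emergency admission or death enter the model only if they happen to predict missingness.

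**Working it through.** **1. Reproduce the sample size.** Inputs from the Sample size section: 3,014 randomised, 90% power, margin 0.05, one-sided 2.5%, 5% loss, and a usual-care rate of 20.7% inflated by 1%, read as one percentage point (p = 0.217). No true difference is assumed.
- n per arm = (1.960 + 1.282)² × 2p(1 − p) / 0.05² = 10.507 × 0.33982 / 0.0025 = 1,428.3, so 1,429.
- Dividing by 0.95 and rounding up gives 1,505 per arm, or 3,010 in total against the stated 3,014.
- Other readings of the event rate fit less well: 20.7% × 1.01 gives 2,930, and 20.7% alone gives 2,906.

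The stated size is therefore an unadjusted calculation.

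**2. Power at the planned size.** 3,014 × 0.95 = 2,863 analysed. The standard error of the risk difference is √(0.33982 / 1,431.65) = 0.01541, and 0.05 / 0.01541 = 3.245. Power = Φ(3.245 − 1.960) = 90.1%.

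**3. How little the screening rests on.** Missing outcomes number 3,014 × 0.014 = 42 at the previous trial's rate and 3,014 × 0.05 = 151 at the allowance. If there were k independent candidates unrelated to missingness, tested at 5%, the chance that at least one enters is 1 − 0.95^k: 23% for k = 5, 40% for k = 10, 64% for k = 20. Both k and the 5% threshold are assumptions; the article gives neither.

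**4. Cost of irrelevant but complete covariates.** Inflating the variance by 1 + q/2,863 for q added covariates gives power of 90.0%, 90.0% and 89.9% for q = 5, 10 and 20. This cost is negligible.

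**5. Cost if a selected covariate is incomplete and its rows are dropped.** The documents give no rate for missing covariates, so a range is shown:

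| Covariate missing | Analysed | Power |
|---|---|---|
| 0% | 2,863 | 90.1% |
| 2% | 2,806 | 89.5% |
| 5% | 2,720 | 88.6% |
| 10% | 2,577 | 86.8% |

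**6. Gain from adjusting for the eligibility scores.** The variance is multiplied by (1 − R²), where R² is the share of outcome variance the scores explain. R² follows from an assumed AUC under a logistic model with a normally distributed risk score at a 21.7% event rate. The documents give no prognostic strength.

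| Assumed AUC | R² | Power at 3,014 | Randomised for the same power |
|---|---|---|---|
| 0.55 | 0.005 | 90.2% | 2,998 |
| 0.60 | 0.022 | 90.7% | 2,948 |
| 0.65 | 0.050 | 91.5% | 2,863 |
| 0.70 | 0.091 | 92.6% | 2,740 |
| 0.75 | 0.146 | 94.0% | 2,573 |

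A simulation of 4,000 trials per setting agrees: 90.0% to 90.3% unadjusted, 90.0% to 90.4% with five irrelevant covariates, and 90.4% to 92.4% with one prognostic covariate of increasing strength.

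**The case against.** Including predictors of missingness is a recognised way to make a missing-at-random assumption more plausible, and it does reduce bias where those predictors also relate to outcome. Selection is on whether the outcome is missing, not on the treatment effect, and the analysis is described as blinded to allocation, so no inflation of type I error is shown. The candidate list, the threshold, the handling of incomplete baseline values and the derivation of the risk difference may all be in the statistical analysis plan. Adjusting for the stratification factors is acceptable in itself. All of this stands, and it limits the point to the entry criterion that the article states.

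A reader might go further and infer any of the following, which the documents do not support:
- **That the whole model is chosen by the screening.** Age, region and site are fixed in advance; only additional covariates are screened. The eFI or STRATIFY risk could themselves enter if they predicted missingness.
- **That omitting the scores costs planned power.** The stated 90% never relied on adjustment.
- **That power will fall to about 87%.** That needs a selected covariate missing in 10% of participants and those rows dropped. The article gives no such rate and does not say which covariates would be candidates.
- **That a gain of two points or more is assured.** STRATIFY predicts hypotension, syncope or falls over 5 years, not all-cause emergency admission or death at 1 year. Selecting on the scores at entry narrows their spread, and only what they add beyond age, region and site counts.

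**Conclusion.** The point holds as a modest weakness in pre-specification, together with a forgone gain in precision. The article adds covariates to the confirmatory model on a criterion that secures neither less bias nor more precision, using tests based on roughly 42 to 151 missing outcomes. If the selected covariates are complete, the effect on power is 0.1 to 0.2 points. It grows only if they are incomplete and nothing is done about it; because planned power is 90.1%, even 2% of rows dropped would then take it just below 90%.

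Naming the eFI and STRATIFY risk in the model would add about 0.2 to 4 power points for an assumed AUC of 0.55 to 0.75, equivalent to about 16 to 441 of the 3,014 participants. The lower part of that range is the more likely. These figures assume a 21.7% usual-care rate, 5% loss, no true difference, and an analysis that carries the gain through to the risk-difference scale.

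**What to change.** Fix the primary model in advance as treatment, age, region, site (random), baseline eFI and baseline STRATIFY risk. From it, report the standardised (marginal) risk difference with its 95% confidence interval against the 5-point margin, so that the adjusted analysis answers the question on the scale of the decision. Move covariates screened for missingness to a sensitivity analysis or to a multiple-imputation model, where their use is legitimate and incomplete values can be handled; the trial already plans multiple imputation for its economic evaluation.

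The cost is a change of wording in the protocol and statistical analysis plan before database lock. The small downside is that the eligibility scores must be exported to the analysis file for every participant.

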### Trial design

This trial uses an individually randomised, controlled, non-inferiority design, based on the trial design successfully tested and implemented in the previous OPTiMISE trial [11, 13, 14]. It aims to establish whether deprescribing antihypertensives is safe in older people, examining the following research questions:What is the effect of deprescribing blood pressure lowering drugs on hospital admissions and death?What is the effect of deprescribing on costs to the NHS and health-related quality of life?

The trial compares step-down medication reduction (withdrawal of one antihypertensive medication at a time, at 4-week intervals, with monitoring of blood pressure at 4 weeks’ visit following each withdrawal) with usual care (no medication reduction mandated). Participants are expected to attend a baseline visit and a 4-week safety visit per antihypertensive deprescribed. Subsequent follow-up data is collected via routine electronic health records and participant questionnaires sent at 1-year post-randomisation. The primary outcome is emergency hospital admission and all-cause death at 1 year. The trial team will also perform a cost-effectiveness analysis to assess the short and long-term impacts of deprescribing antihypertensives.

This trial is undertaken in a primary care setting, within approximately 200 general practices across all regions of the NIHR Research Delivery Network in England. The primary care setting enables all potentially eligible participants to be identified and approached, and permits examination of the intervention, in the setting in which it will be delivered in routine clinical practice.

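### Secondary-outcome models omit region, a randomisation stratification factor that the primary model includes: a minor, unexplained inconsistency with a very small cost in precision

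*Protocol article*

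**What the plan says.** Under Baseline assessments, the protocol article describes individual 1:1 allocation by stratified randomisation "with stratification factors age (i.e. 75–79 and ≥ 80 years) and region of England", with permuted blocks inside the strata.

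Under Statistical methods for primary and secondary outcomes, the primary model follows that design: "The model will include age and NHS England region as fixed effects and site as a random effect". The next paragraph sets the secondary models: "Generalised linear models adjusting for age as a fixed effect and site as a random effect will be used for secondary outcomes". Its list of examples runs from falls, syncope, fracture, stroke, MI and adverse drug withdrawal events (ADWEs) to continuous measures such as blood pressure and quality of life. It includes all-cause death and hospitalisation or death. All-cause emergency hospitalisation is a secondary outcome under Trial outcomes.

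The article gives no reason for leaving region out, and no other section puts it back.

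**The concern.** A factor used to stratify the randomisation is normally carried into the analysis. Stratifying balances the arms on that factor. A model that leaves it out counts the variation it explains as noise, so in a linear model the reported standard error is larger than it need be. Here one stratification factor (age) is kept and the other (region) is dropped, which follows no evident principle.

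The second issue is coherence of reporting. Readers will ask whether the composite is driven by deaths or by admissions. As written, the composite is adjusted for region and its components are not.

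This is not a matter of detail left to the statistical analysis plan. The article names a specific covariate set for the secondary models, and an analyst who follows it would fit them without region.

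**Working it through.** **Covariates side by side**

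| | Age | Region | Site |
|---|---|---|---|
| Randomisation strata | yes | yes | no |
| Primary model | fixed | fixed | random |
| Secondary models | fixed | not listed | random |

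I take the region used for stratification and the NHS England region in the primary model to be the same factor.

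**The plan's own figure.** The article gives no number for this point. Its sample size serves only as an input. With a control rate of 20.7% + 1 point = 21.7%, a margin of 0.05, one-sided 2.5% and 90% power: n per arm = 2 × 0.217 × 0.783 × (1.960 + 1.282)² / 0.05² = 1,429. The total is 2,858, and 2,858 / 0.95 = 3,009, against 3,014 stated. Adding region to the secondary models does not touch this figure.

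**Inputs for the size of the effect**
- From the article: 3,014 participants (Sample size) and about 200 practices (Trial design), so 3,014 / 200 ≈ 15 per practice.
- Assumed, not in the article: continuous outcome, residual variance 1, site variance 0.04 (SD 0.2 of the residual SD), region variance 0.01 or 0.04. The region shares of total variance are 0.01 / 1.05 = 1.0% and 0.04 / 1.08 = 3.7%.

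**Formula.** Allocation is not blocked by practice. With m participants per practice and between-practice variance t, the information on the treatment effect per practice is proportional to (m − 1) + 1 / (1 + m t). The first term is the within-practice comparison, which region cannot affect. The second is the between-practice part. With region in the model, t is the site variance. Without it, t becomes roughly site plus region variance.

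**Results, m = 15**
- Region in the model: 14 + 1 / (1 + 15 × 0.04) = 14.625.
- Region omitted, region variance 0.01: 14 + 1 / (1 + 15 × 0.05) = 14.571. SE ratio = √(14.625 / 14.571) = 1.002.
- Region omitted, region variance 0.04: 14 + 1 / (1 + 15 × 0.08) = 14.455. SE ratio = √(14.625 / 14.455) = 1.006.

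The excess is therefore 0.2% to 0.6%. With no site term at all, 1 / √(1 − R²) at the same shares gives 1.005 and 1.019, so the site effect removes most of the excess.

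**Sensitivity to the site variance.** If practices did not differ at all beyond region (site variance 0), the ratios would be √(15 / 14.870) = 1.004 and √(15 / 14.625) = 1.013. The excess is still about 1% or less.

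**Cross-check by simulation.** The simulation used N = 3,014, 200 sites in 12 regions, region and site SD both 0.2 of the residual SD, stratified blocks of 4 and 150 replicates. All settings except N and the number of sites are assumed.

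| Model | Mean SE | Rejection under the null |
|---|---|---|
| Region + site | 0.0368 | 4.7% |
| Site only (as planned) | 0.0370 | 4.7% |
| Neither | 0.0378 | 3.3% |

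0.0370 / 0.0368 = 1.005, in line with the formula. Many of the mixed-model fits gave convergence warnings, so these figures indicate scale only.

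**Could region be added to every model?** The article does not give the number of regions. At an assumed 1% event rate, 12 regions give 3,014 × 0.01 / 12 = 2.51 expected events per region. The chance that a given region has none is e^(−2.51) = 0.081, and the chance that at least one region has none is 1 − (1 − 0.081)^12 ≈ 64%. With 7 regions the expectation is 4.31 and the chance is 1 − (1 − e^(−4.31))^7 ≈ 9%.

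**The case against.** The strongest reply is that the planned secondary models are already adjusted for geography. Practices lie within regions, so a site random effect carries regional differences. This largely stands. A reader might infer that the analysis discards the stratification, or that standard errors are too wide by 0.5% to 1.5%, the range that 1 / √(1 − R²) gives for R² of 1% to 3%. That formula describes a model with no site term, which the article does not propose. The absorption is not complete, because a random intercept on about 15 participants is shrunken. The reply also does not explain why the primary model has both terms.

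A second reply is that the linear formula does not fit most of the listed outcomes, which are proportions. This stands too. The article names no link for them. Under a logit link, adding a prognostic covariate generally does not shrink the standard error of the log odds ratio, and leaving it out moves the conditional estimate towards the null. The 0.2% to 0.6% therefore applies to linear and risk-difference models only.

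A third reply concerns comparability. A reader might infer that the composite and its components would estimate different things. For a marginal risk difference they would not, because that measure is collapsible and adjustment changes its precision only. The article defines the primary effect as an absolute risk difference and does not say that the components use another measure. What remains is an unexplained difference in method.

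Finally, a leaner model is defensible for rare events, where a region without events has no finite logit coefficient. This stands and limits the fix. That the article is condensed does not remove the inconsistency, since it states both covariate sets, but the full protocol may resolve it.

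**Conclusion.** The inconsistency is real and minor. Region is a stratification factor, the primary model includes it, and the stated secondary models do not. For linear or risk-difference models the cost is a standard error about 0.2% to 0.6% too wide. This rests on assumed region shares of about 1% to 4% of variance, a site SD of 0.2 of the residual SD and about 15 participants per practice. There is no bias on those scales, and null rejection in the indicative simulation was the same with and without region.

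The primary non-inferiority conclusion, the sample size and the error rate are unaffected. A reader might infer from the mismatch that the safety conclusions are at risk; nothing in the document supports that. The case for acting rests on consistency between the composite and its components and on the low cost of the change.

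**What to change.** In the sentence on secondary outcomes, add NHS England region as a fixed effect, so that age, region and site match the primary model. Do this at least for the components of the composite (all-cause death, emergency hospitalisation) and for the continuous outcomes. For sparse outcomes such as MI, stroke or ADWE, pre-specify that region is dropped, and age and site kept, where the region terms cannot be estimated. If region was left out on purpose, state the reason instead. Since these models contain a random effect, they should also be called mixed models.

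The cost is one sentence, a few extra parameters per model and possible non-convergence for rare events, which the fallback covers.
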